The war in Ukraine brings new challenges to primary care and mental health services all over Europe. We focus on perinatal mental health, and to our knowledge, no previous studies have been conducted to study the impact of war in this field. Although for most European citizens, the date of the war outburst is 24 February 2022, the war in Ukraine, with all the consequences for the civil population, including pregnant and postpartum women, started in 2014. A study conducted in 2016 (Ancheva and Morozova, 2016) demonstrated PTSD frequency in 34.8% of pregnant women displaced internally. Another study showed an increased risk of reactive and personal anxiety, depressive manifestations, autonomic dysfunction, insomnia (Romanenko, 2020), and the risk of premature termination of pregnancy among war-affected population (Cox et al., 1987; Romanenko, 2020). Pregnant women who have been forced to relocate within their own country display a high amount of both reactive and personal anxiety. In pregnant women who were internally displaced, reactive anxiety was 3.3 times higher, and personal anxiety was 2.6 times higher than in pregnant women who were not internally displaced (Zhabchenko et al., 2018). However, to date, there are no publications on changes in the mental health of pregnant women and mothers of newborn children during the full-scale war in Ukraine. The research team intends to launch an international longitudinal study in order to address the lack of knowledge on the consequences of the war and the status of war refugees on maternal mental health during pregnancy. This article outlines the design of the study.

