### Symptoms

Another objective is to evaluate possible risk and protective factors (including social and economic factors, personality traits, social support, and access to medical/mental health services). We are focusing on the two groups of women who were affected by war during pregnancy: those who left Ukraine and are now refugees in other European countries (known as external refugees) and those who chose to remain in Ukraine (in the same place of residence, considered as internal refugees).

The main goals are the following:To evaluate how perinatal mental health has been affected during the war, by observing the differences in (a) levels of depression, anxiety, post-traumatic stress disorder, and birth trauma; as well as in (b) clinical risk indices (proportion of women above the clinical cut-off point on a validated self-report scale)To research which risk and protective factors have a bearing on perinatal mental health during the war.To examine the links between pregnancy results and mental health of women in war-affected areas.To examine the experiences during the birth and delivery, specifically the potential traumatic events during this period.To assess the perinatal women’s needs concerning support and mental health services in Ukraine and in the host countries.

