## Methods

### Study design

This is an international observational cohort study. The rationale is to evaluate women’s perinatal mental health experiences throughout pregnancy and the first year after childbirth. The general study will extend from 01 December 2022 to 30 June 2023. This date can be changed depending on the situation of the war.

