### Participants

The research sample consists of females in the time around childbirth. To be included in the study at the beginning, participants must meet the following criteria:Being pregnant or a biological mother of an infant up to 12 months of age.Being 18 years or older.Being a war refugee from Ukraine (entrance to EU countries from 24 February 2022) or staying in Ukraine after/during the war.Consenting to take part in the study.

The exclusion criteria are:Not being currently pregnant or not being the biological mother of an infant up to 12 months of age.Younger than 18 years of age.Not consenting to take part in the study.

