### Ethical standards

This study has been conducted in accordance with the protocols stated in the Declaration of Helsinki. Ethical authorization was given (21-PSI-2022). All national guidelines for data security are followed in the management of study data. Digitalized informed consent will be received from all members, and the confidentiality of all the data will be protected. The study design has been preregistered in ClinicalTrials.gov (ref: NCT05654987) following gold standards in research on cross-sectional studies, STROBE (Vandenbroucke et al., 2007).

Participation in the study can elicit changes in one’s emotional state. To address this specific problem, at the end of the survey, a list of up-to-date services and resources will be provided where the participants can obtain information and help concerning mental health services and lactation advice. In addition, contact details of the lead research team for each nation will be available if participants wish to seek out further information. On request, the researchers will provide the participants with the global results of the study.

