### Data analysis

#### Descriptive

At the beginning, descriptive statistics will be examined for all the study variables. To analyze the presence or not of the different variables (depression, anxiety or PTSD) concerning the different categorical variables, contingency tables will be made using *Pearson’s Chi-Square*. *Cramer’s V* will be used to calculate the effect size. Likewise, when the variables are continuous, Student’s *t* will be used, and the effect size will be calculated using Cohen’s *d.*

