## Conclusion

To sum up, this study is an international research project created to evaluate the effect of the Ukrainian War on the mental health of women during pregnancy. It will allow for a thorough overview of how the war has affected mental wellbeing during the perinatal period, which could then be used to support and guide refugees and providers in different situations. Ultimately, this research should provide concrete data for policymakers and healthcare professionals to utilize.

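### Goal 1 and the conclusion claim to show how the war affected mental health, but a wholly war-affected sample, conflicting design labels and unadjusted comparisons of symptom levels support only description and association

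*Protocol article*

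**What the plan says.** **Goal.** Under Symptoms, goal 1 is "To evaluate how perinatal mental health has been affected during the war, by observing the differences in" (a) levels of depression, anxiety, post-traumatic stress and birth trauma and (b) proportions above a clinical cut-off. It does not say between whom, or between which times, the differences are taken. The Conclusion goes further: "It will allow for a thorough overview of how the war has affected mental wellbeing during the perinatal period". The Abstract likewise speaks of the war's impact.

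**Who is studied.** "We are focusing on the two groups of women who were affected by war during pregnancy": those who left (external refugees) and those described as having chosen to remain (internal refugees). The matching inclusion criterion under Participants is "Being a war refugee from Ukraine (entrance to EU countries from 24 February 2022) or staying in Ukraine after/during the war".

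**Design labels.** The Abstract and Study design say cohort. The Introduction says "The research team intends to launch an international longitudinal study". Ethical standards describes a design preregistered "following gold standards in research on cross-sectional studies, STROBE". Study design gives the rationale as evaluating women's "mental health experiences throughout pregnancy and the first year after childbirth", in a window from 1 December 2022 to 30 June 2023 that may change with the war. Procedure describes one baseline questionnaire of about 35 minutes.

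**Analysis.** Under Descriptive: "To analyze the presence or not of the different variables (depression, anxiety or PTSD) concerning the different categorical variables, contingency tables will be made" with Pearson's chi-square, and Student's t for continuous variables. The prediction-model text that follows plans regularized logistic regression, random forest, decision tree and gradient boosting for depression, anxiety or PTSD, with removal of terms by p-value, and then forward stepwise logistic regression.

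**The concern.** Three features bear on what goal 1 can deliver. First, an effect of the war needs a contrast with women not exposed to it, or with a time before it, and the article names neither. Second, a cohort or longitudinal label leads readers to expect follow-up, and none is described. Third, the one contrast plainly available, internal versus external, compares groups formed partly by the women's own decisions, yet the tests stated for it are unadjusted.

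The results are meant for policymakers. Followed as written, the report could present an internal/external gap as the war's doing when part of it reflects who left and who stayed.

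**Working it through.** **1. The article's own planning figure.** Sample size gives a minimum of 300 from alpha 0.05 and 50% variability, with no margin of error, so 300 cannot be reproduced. With n = z²p(1−p)/e², z = 1.96 and p = 0.5:
- e = 5 points gives 1.96² × 0.25 / 0.05² = 384.2, so 385.
- n = 300 corresponds to e = 1.96 × √(0.25/300) = 5.66 points.

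These inputs suit the precision of one prevalence. They do not address a between-group difference or a change over time.

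**2. Labels against the described assessment.** Three labels (cohort, longitudinal, cross-sectional) sit beside one described assessment. The window is 31 + 31 + 28 + 31 + 30 + 31 + 30 = 212 days, about 7 months. Pregnancy plus the first year is about 9 + 12 = 21 months, so the stated window could follow any one woman over about a third of that period at most.

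**3. Comparator.** Both named groups are war-affected, and eligibility admits no one else. War exposure is a listed predictor in Table 1, so a gradient over exposure can be estimated within the sample. That gradient is an association, because exposure was not assigned. No sample size turns a comparison of two war-affected groups into a comparison with no war.

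**4. Do the multivariable models supply the adjusted contrast?** Set against goal 1:
- Purpose: they are introduced for risk and protective factors, which is goal 2.
- Outcomes: they predict depression, anxiety or PTSD as dichotomies. Goal 1(a) concerns levels and includes birth trauma, and no adjusted analysis is stated for continuous scores or for birth trauma.
- Terms: the predictors in Table 1 include neither displacement group nor perinatal stage.
- Selection: backward removal at 0.05 and forward selection can each drop the group term or a confounder.

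For group differences in symptom levels, the stated tests are therefore the unadjusted ones.

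**5. Illustrations of confounding (all inputs assumed, none from the article).**
- Prevalence 20% in pregnant and 30% in postpartum women in both groups; pregnant share 60% in one group and 30% in the other. Crude prevalences: 0.6 × 20 + 0.4 × 30 = 24% and 0.3 × 20 + 0.7 × 30 = 27%. The gap is 3 points with no true difference. With 150 per group, SE = √(0.24 × 0.76/150 + 0.27 × 0.73/150) = 5.0 points, so the gap is about 0.6 SE.
- A binary risk factor held by 60% versus 30% that raises prevalence by 20 points: (0.6 − 0.3) × 20 = 6 points. With 150 per group and 30% versus 36%, an unadjusted two-sided 5% test rejects about 20% of the time.

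**The case against.** The strongest reply has four parts.

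- **The plan is not only unadjusted.** This is correct. A reader might infer from the Descriptive section that nothing else is done, but that section is a first step, does not itself name the internal/external contrast, and is followed by multivariable models that include war exposure and earlier mental health. What remains is narrower: those models do not name displacement group and do not cover levels or birth trauma.
- **Later waves may exist.** The words baseline and longitudinal hint at them, and a condensed article may leave them to the full protocol. A reader might infer that no within-woman change will ever be observed, or that the study is simply cross-sectional; the article's silence does not prove either. The reference to pregnancy and the first year can also mean coverage of stages across different women, and none of the five goals is within-woman change. The conflict between labels stands, because it is stated text.
- **Goal 1 can be answered descriptively.** The Aim section is worded as exploration, and goal 1 lists levels and proportions straight after the two groups are named. A reader might infer that goal 1 cannot be answered at all. That goes too far: only the causal reading fails. The Conclusion nevertheless uses the causal reading.
- **The illustrations rest on invented inputs.** They do, and the 3-point gap lies well inside sampling noise at 150 per group. The article gives no data on how the groups differ, only that some women chose to remain.

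**Conclusion.** The point holds as a limit on what the study can conclude. The design labels conflict, and one questionnaire is described. With only war-affected women eligible and no reference named, within-sample differences support description and association, not the war's effect. The stated tests for group differences in symptom levels are unadjusted, and the prediction models do not fill that gap.

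The size of any confounding is unknown. The 3-point and 6-point gaps show the mechanism under assumed figures and estimate nothing. The verdict assumes that the full protocol contains no external or pre-war reference and no prespecified adjusted comparison. If it contains either, the article should say so, since its goal and conclusion depend on it.

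**What to change.** 1. **Reconcile the labels.** Use cross-sectional throughout if no later wave is planned. Otherwise keep cohort or longitudinal and state the waves and their timing.
2. **Restate goal 1 and the Conclusion.** The targets become symptom levels and proportions above cut-off, their internal-versus-external difference, and their gradient over war exposure. Make no claim about the war's effect unless an external or pre-war reference is named.
3. **Prespecify the internal/external contrast.** Use linear regression for scores, including birth trauma, and logistic regression for the dichotomies. Put displacement group and a fixed covariate set in the model and keep them there without p-value selection: perinatal stage, age, education, parity, prior mental illness and survey date, as collected. Keep the chi-square and t-tests as descriptive.

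**Cost.** A more modest headline claim and slightly more analysis. The article already lists education, prior pregnancies, residence and earlier mental health as recorded. Age and perinatal stage underlie eligibility but are not among the questionnaire items named, so the authors should confirm that both are stored as variables.

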### Edinburgh postnatal depression scale

The Edinburgh Postnatal Depression Scale (EPDS; Cox et al., 1987) is the most widely used self-assessment tool designed to recognized women at risk for perinatal depression (Hahn-Holbrook et al., 2017 < NICE. National Institute for Health and Care Excellence, 2017). This scale includes 10 items measuring common symptoms of depression and anxiety. The scores range from 0 to 30. The cut-off values of 10 or higher and 13 or higher are most often used to identify women who are at risk for depression (Levis et al., 2020). However, 13 has been shown to be the most useful cut-off point established in previous studies. The positive predictive value of EPDS is estimated to be 70% (Cox et al., 1987) or even 90% (Levis et al., 2020). A systematic review has also shown that the EPDS has good psychometric properties in low and middle countries (Shrestha et al., 2016). The EPDS has been validated in over 60 languages (Cox et al., 1987; Gibson et al., 2009; Cox, 2019; Vázquez and Míguez, 2019; Levis et al., 2020). The Ukrainian version, “Единбурзька шкала післяпологової депресії (ЕШПД)” was translated by the study authors.

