### Generalized anxiety disorder screener, GAD-7

The GAD-7 (Spitzer et al., 2006) is a 7-item instrument that assesses each of the seven symptoms of general anxiety disorder. The GAD-7 screens for anxiety symptoms in the general population and according to the criteria established by the Diagnostic and Statistical Manual of Mental Disorders (DSM)-IV and DSM-IV-TR (American Psychiatric Association, 1994; American Psychiatric Association, 2000). The GAD-7 total score ranges from 0 to 21. The scale’s total score indicates the level of anxiety symptoms, with higher scores reflecting a greater anxiety severity. Scores of 5, 10, and 15 represent cut-off points for mild, moderate and severe anxiety, respectively (Spitzer et al., 2006). When screening for an anxiety disorder, a recommended cut-off point for referral for further evaluation is 10 or greater (Spitzer et al., 2006). The Ukrainian version of the GAD-7 is available (Romanchuk, 2011) but no psychometric properties have been studied yet. The GAD-7 has shown good psychometric properties during pregnancy (Soto-Balbuena et al., 2021) and the postpartum period (Simpson et al., 2014; Fairbrother et al., 2019).

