### Impact of events scale-revised

The Impact of Event Scale-Revised (IES-R; Weiss and Marmar, 1997) is a self-assessment tool measure for capturing the level of symptomatic response to specific traumatic stressors as it was manifested in the previous 7 days.

The scale has been translated into different languages (Baguena et al., 2001; Asukai et al., 2002) and different samples (Beck et al., 2008) with good psychometric properties.

A revised version of the Impact of Event Scale-Revised by Weiss and Marmar (1997), contains 22 items with scores gathered using a 5-point scale (0–4). What differentiates this revised version of the Impact of Event Scale (IES-R) from the previous one is that this latest version has seven additional questions and a scoring range of 0 to 88.

On this test, a score of 24 or more is clinically significant as it is indicative of an individual having full or partial PTSD. A score of 33 or more is the most accurate way to determine the probability of PTSD, and a score of 37 or higher is a strong indication of the disorder (Weiss, 2007).

This questionnaire considers the three dimensions of PTSD according to DSM-IV (Weiss and Marmar, 1997), including the following: Intruding recurring images, dreams, and/or thoughts or perceptual impressions related to the traumatic event; Agitation characterized by increased alertness, anxiety, impatience, and/or difficulty concentrating attention; and Avoidance manifested by efforts to get rid of thoughts, emotions, or conversations related to the traumatic event.

The Ukrainian version “Шкала впливу стресових подій – переглянута (ШВСП-П)” was translated into Ukrainian by the study authors.

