### Translations of the measures

Three instruments were translated to Ukrainian in this study. The Edinburgh Postnatal Depression Scale (Cox et al., 1987) was translated by [name], [name], and [name] The City Birth Trauma Scale (Ayers et al., 2018) was translated by [name], [name], [name], and [name] The impact of events scale-revised (Weiss and Marmar’s, 1997) was translated by [name], [name], and [name] The translation was carried out according to Brislin’s translation model (Brislin, 1970; 1986), applicable to the preparation of instruments for cross-cultural research. The back translations were carried out, and the detailed procedure of the translations is available from the authors.

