#### Psychometric properties

To examine the psychometric properties of the questionnaires in the Ukrainian language, several analyses will be reported. Exploratory Factor Analyses (EFA) will be conducted using Statistical Package for the Social Sciences (SPSS), Version 26 software. Analysis of the factor dimensional constraints will determine each model’s underlying individual item loadings. Based on the results of the EFA, Confirmatory Factor Analysis (CFA) will then be analyzed. ECA will be used to analyze how to fit the models using several indexes such as Satorra-Bentler χ^2^, CFI, RMSEA and the confidence interval of RMSEA statistics will be calculated. Lagrange multipliers and Wald test will be sequentially performed to improve the models’ fitness, following the study’s hypotheses. Standardized coefficients and measurement equations with scores in R2 will be reported. These analyses will be conducted using the AMOS program.

Prediction models. To examine the risk and protective factors associated with perinatal mental health outcomes, a random sample of 70% of participants will be used to derive the machine learning algorithms, including regularized logistic regression, random forest, decision tree, and gradient boosting to predict the risk of perinatal mental health outcomes, and their performance, and the remaining 30% for validation. First, in the derivation sample, all predictors described above will be included in the models to estimate the probability of depression, anxiety, or PTSD. Beginning with a model containing all potential covariates, the variable with the least significant *p* value will be removed and tested using the likelihood-ratio test until all variables left in the model significantly (at alpha = 0.05) contributed to the model.

In regularized logistic regression models, results will be presented as Odds Ratio (OR) with 95% confidence intervals (CIs).

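### Goal 1(b) counts women above a cut-off on a validated scale, but no cut-off is shown to be validated in the Ukrainian versions used, and the planned factor analyses cannot validate one

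*Protocol article*

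**What the plan says.** The list of main goals (under the heading Symptoms) gives goal 1 two parts. Part (a) compares levels of depression, anxiety, post-traumatic stress and birth trauma. Part (b) concerns clinical risk indices, defined as the "proportion of women above the clinical cut-off point on a validated self-report scale".

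The measures sections describe the versions to be used:

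- Translations of the measures: "Three instruments were translated to Ukrainian in this study". These are the EPDS, the City BiTS and the IES-R. The EPDS section says the same of its Ukrainian version, which "was translated by the study authors".
- GAD-7: a Ukrainian version exists, "but no psychometric properties have been studied yet".
- TIPI: a Ukrainian adaptation is cited, but this is a personality measure and the article gives no clinical cut-off for it.

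The Descriptive section of the analysis begins its categorical comparisons with "To analyze the presence or not of the different variables (depression, anxiety or PTSD". The prediction models, described under Psychometric properties, are meant "to estimate the probability of depression, anxiety, or PTSD". The Discussion describes the study as one that investigates prevalence.

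**The concern.** A cut-off is a property of a particular language version, checked against a clinical reference. Goal 1(b) claims that property, and the measures sections do not show it for any of the four symptom scales. The analysis then drops the distinction between scoring above a threshold and having a disorder.

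The Conclusion offers the results to policymakers and healthcare professionals. A screen-positive rate labelled as presence or prevalence of disorder can be set directly beside the prevalence figures for PTSD, major depression and generalized anxiety disorder that the Introduction cites. It is not the same quantity.

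**Working it through.** The defect is one of definition, so the main check sets the sections side by side.

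**Step 1: status of each version and its threshold, as the article gives them.**

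| Scale | Ukrainian version | Threshold given |
|---|---|---|
| EPDS | new, by the study team | 10 and 13; 13 favoured, from earlier studies |
| GAD-7 | exists, psychometrics unstudied | 5, 10, 15 for severity; 10 for further evaluation |
| IES-R | new, by the study team | 24, 33, 37; 33 called the most accurate |
| City BiTS | new, by the study team | none; only percentiles (3, 9, 18) |

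The first IES-R threshold reads "On this test, a score of 24 or more is clinically significant". All four versions are new or untested. For City BiTS there is no cut-off to apply, although birth trauma belongs to goal 1.

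**Step 2: can the planned psychometrics fill the gap?** The Psychometric properties section plans exploratory factor analysis, then confirmatory factor analysis with fit indices. These show whether the items group as expected. Validating a cut-off needs sensitivity and specificity against an independent case definition. Table 1 and the Procedure section describe an online self-report questionnaire and no diagnostic interview. The ROC curves at the end of the analysis plan assess the prediction models. The only case status described for those models is the scale-based one, so they cannot test the scale against a diagnosis.

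**Step 3: does a positive screen equal a disorder on the article's own figures?** "The positive predictive value of EPDS is estimated to be 70" per cent, or 90% in a second source. The share of positives without the disorder is 1 − PPV:

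- 1 − 0.70 = 0.30
- 1 − 0.90 = 0.10

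So 10% to 30% of EPDS positives in those settings, with established versions, would not be cases. The GAD-7 section likewise ties a score of 10 to further evaluation, not to a diagnosis.

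**Step 4: can the bias be sized?** The apparent rate is Se × p + (1 − Sp) × (1 − p). The article gives no sensitivity (Se) or specificity (Sp) for any Ukrainian version, so the values below are assumptions chosen only to show the range. For p, take the 25% for major depression cited in the Introduction:

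- Se 0.90, Sp 0.70: 0.90 × 0.25 + 0.30 × 0.75 = 0.450, which is 20 points too high.
- Se 0.80, Sp 0.90: 0.80 × 0.25 + 0.10 × 0.75 = 0.275, which is 2.5 points too high.
- Se 0.70, Sp 0.95: 0.70 × 0.25 + 0.05 × 0.75 = 0.2125, which is about 4 points too low.

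The sign changes within plausible inputs. The document therefore fixes neither the direction nor the size of the bias.

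**The case against.** Much of the text is careful. Goal 1(b) speaks of risk indices, Table 1 lists symptoms, and the EPDS section refers to women at risk. Validated can fairly describe the original instruments: the EPDS is said to be validated in over 60 languages, and the GAD-7 to perform well in pregnancy and postpartum. The team translated with back-translation, states openly which versions are new, and plans psychometric work. Goal 1(a) uses score levels and needs no cut-off.

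All of that stands, and it limits the point to the words validated, presence, probability and prevalence. It does not remove it. The article does not name Ukrainian among the 60 languages, the EPDS version used is the team's own, and back-translation addresses wording and not thresholds. The softer language elsewhere is a reason to bring the analysis sections into line with it.

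Three stronger inferences are tempting and are not supported:

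- A reader might infer that three IES-R thresholds leave the PTSD rate wide open. The article marks 33 as the most accurate, as it marks 13 on the EPDS. The thresholds mean different things, and the formal choice may sit in an analysis plan not shown.
- A reader might apply the EPDS predictive value to the 28.2% risk rate that the Introduction cites, to count false positives among 300 women. That rate comes from a study in Syria and the predictive values from other samples. Predictive value depends on prevalence, so the product says nothing reliable about this study.
- A reader might infer that the Ukrainian rates will be too high. Predictive value ignores missed cases, so the direction is unknown.

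**Conclusion.** The point holds as a mismatch between what goal 1(b) claims and what the measures and analysis sections provide. No cut-off is shown to be validated in the Ukrainian version used, the planned factor analyses cannot validate one, and the binary outcomes are positive screens labelled as disorder.

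The only size the document supports is the 10% to 30% of EPDS positives without the disorder, for established versions in other samples. For the Ukrainian rates no figure can be given. The conclusion assumes that the condensed article has not left out a diagnostic reference standard; Table 1 lists none. The study remains feasible and its score comparisons are not in question, but the wording should be corrected before rates are reported.

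**What to change.** 1. In goal 1(b), write: *proportion of women scoring at or above the published cut-off of the original scale (cut-off not yet validated for the Ukrainian version used)*. If a Ukrainian validation against a reference standard exists for a version used, cite it instead.
2. In the data analysis sections and the Discussion, call the binary outcomes *screen-positive* for depression, anxiety or PTSD symptoms. Do not report them as presence or prevalence of disorder.
3. Report EPDS ≥13, GAD-7 ≥10 and IES-R ≥33, the values the article itself favours. Show EPDS ≥10 and IES-R ≥24 and ≥37 in one sensitivity table. These are reporting thresholds only and do not bear on the care of participants.
4. Analyse City BiTS as a continuous score, since only percentiles are given.

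The cost is edited wording, one extra table from data already planned, and a more modest claim. No new data collection is needed.
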